### Intervention program

We developed a new gratitude intervention program using the following steps. First, we systematically reviewed RCT studies examining gratitude intervention in workers. The first author then developed a preliminary program in consultation with experts about the occupational stress model, positive psychology, and work engagement. Next, the first author conducted hearing with 5 researchers familiar with gratitude intervention and modified the program according to their recommendations. Lastly, we conducted a 2-week pilot trial with workers nested in one organization (n = 28). The program was finalized after modifications based on the findings. The newly developed gratitude intervention is a 4-week program implemented at an organizational level (Fig. 2). It consists of 3 elements: psychoeducation, gratitude lists, and behavioral gratitude expression (Table 1). Psychoeducation is delivered during week 1 and lasts 1 week. Gratitude lists and behavioral gratitude expressions are completed over the next 3 weeks (weeks 2–4). Gratitude lists and behavioral gratitude expression correspond to increasing personal and job resources, respectively. Psychoeducation will provide a program overview and help participants complete the activities. Details of each component follow.

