### Control group

Participants belonging to the control group will not receive any intervention programs until they complete the 6-month follow-up survey. Then control group participants will receive the intervention program.

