### Sample size calculation

The target sample size was calculated by accounting for intraclass correlations (ICC) of the organizations’ outcomes, according to the guidelines in the Consolidated Standards of Reporting Trials (CONSORT) for cRCTs [47]. Sample sizes in cRCTs should be multiplied by design effect (1 + [m − 1]ρ), where m is the average cluster size, and ρ is ICC. In a previous study, ICC for work engagement among Japanese employees was 0.09 [48]. The cluster size was set to 20 [49]. An effect size of the individual intervention program was estimated at 0.30 based on a previous meta-analysis on well-being [39, 50]. Based on these estimations, 637 participants from 32 organizations per arm will be needed at an alpha error rate of 0.05 and a beta error rate of 0.10 using G*Power version 3.1.9.2 [51, 52].

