### Randomization

Companies participating in the study will select organizations to participate in the program. Although the coordinator will choose the organizations, if necessary, the first author and the coordinator will discuss how to select or classify the organization. The selected organizations will then be randomly assigned to the intervention or control group in a 1:1 ratio within the company unit. Permuted block randomization (block size = 2) will be adopted for equal randomization. For example, if 4 organizations in a company participate, 2 will be assigned to the intervention group and 2 to the control group. Assignments will be made after all participating employees have responded to the baseline survey (T1). All data related to randomization (company and organization lists and random number tables) will be password-protected. Research assistants not involved in program administration or results analyses and who are blind to the researchers (YK, KW, and NK) will carry out the entire randomization process. Because of the nature of the intervention, it is not possible to blind the person implementing it.

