#### Statistical analysis

Primary analysis of the intervention program’s effects on work engagement will be carried out by multilevel latent growth modeling (LGM) [53] using robust maximum likelihood estimation. This study will examine repeated measures for employees at level 1, work engagement within employees at level 2, and interactions within organizations at level 3. We will compare the significance of the dummy-variable coefficient for the intervention (control = 0, intervention = 1), with the linear slope of work engagement representing the intervention program’s effect. We will reference some model fit indices, such as χ^2^, the comparative fit index (CFI), the Tucker–Lewis index (TLI), and root mean square error of approximation (RMSEA). We will then determine the model that demonstrates a good fit based on the fit indices, specifically CFI and TLI greater than 0.95 and RMSEA smaller than 0.06 [54]. Intention-to-treat (ITT) analysis using full information maximum likelihood estimation will be conducted, including all employees who complete the baseline survey. If the LGM yields misspecified or improper solutions, we will consider running a three-level mixed-model analysis using restricted maximum likelihood estimation. If no data hierarchy is found in the organizational analysis (e.g., ICC is not significant or less than 0.05) [55], we will consider analyzing the data individually. Mplus Version 8 [56] and PASW Statistics 20 will be used for LGM and mixed model analysis, respectively. The analysis of secondary outcomes (gratitude at work, self-efficacy, sense of coherence, support from supervisors and coworkers, eudaimonic well-being at work, psychological distress, and work performance) will be conducted using the same methods. Potential subgroup analyses will be conducted, stratified by degree of commitment to the program (numbers of gratitude lists and behavioral gratitude expressions) and initial work engagement levels or gratitude at work. Some mediation analyses will also be conducted using multilevel structural equation modeling.

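### Degree of commitment, a post-randomization variable with no control-arm value, is listed as a subgroup factor; an effect stratified by it has no randomized comparator and can mimic a dose-response

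*Protocol article*

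**What the plan says.** Four parts of the protocol article bear on this.

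- **Statistical analysis.** After the primary and secondary analyses, the article states: "Potential subgroup analyses will be conducted". They are to be "stratified by degree of commitment to the program (numbers of gratitude lists and behavioral gratitude expressions"), and the same sentence continues "and initial work engagement levels or gratitude at work". One list therefore holds a measure of program use and two baseline measures. The article gives no method for the commitment strata and no caution about causal reading. The primary analysis is intention-to-treat, "including all employees who complete the baseline survey".
- **Intervention program.** "Gratitude lists and behavioral gratitude expressions are completed over the next 3 weeks", that is, in weeks 2–4 (also Table 1).
- **Randomization.** "Assignments will be made after all participating employees have responded to the baseline survey (T1"). Allocation thus precedes the tasks that are counted.
- **Control group.** Controls "will not receive any intervention programs until they complete the 6-month follow-up survey".

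**The concern.** A subgroup effect is a difference between arms among people of the same kind. That requires a variable fixed before allocation, or at least unaffected by it, and known in both arms. Initial work engagement and initial gratitude at work meet this. The number of lists and messages does not: it arises after allocation and has no counterpart among controls during the 6 months of follow-up. No control stratum corresponds to the high-commitment employees.

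Two contrasts remain: high-commitment employees against all controls, or against low-commitment employees in the same arm. In both, the groups are partly self-selected. Selection related to the outcome is plausible here, because the primary scale measures vigor, dedication and absorption at work, and employees who score well or are improving may complete more voluntary work-related tasks whatever the program does.

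What is at stake is the reading of the result. A gradient across commitment levels invites the conclusion that the program works for those who do it, and this design cannot show that by stratification.

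**Working it through.** **The plan's own figure.** The only design figure that serves as a yardstick is the standardized effect of 0.30 in the Sample size calculation section, and the calculation built on it reproduces.

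- Inputs: effect 0.30, ICC 0.09, cluster size 20, and the sample "needed at an alpha error rate of 0.05 and a beta error rate of 0.10". Sidedness is not stated.
- Two-sided two-sample t-test: 235 per arm.
- Design effect: 1 + (20 − 1) × 0.09 = 2.71.
- 235 × 2.71 = 636.85, rounded up to 637 per arm; 637 / 20 = 31.85, rounded up to 32 organizations.
- A one-sided test would give 191 × 2.71 = 517.6, so the stated 637 is two-sided.

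Nothing in that calculation is disputed.

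**Timing.** The order is baseline survey, allocation, psychoeducation (week 1), lists and messages (weeks 2–4), surveys at 1, 3 and 6 months, and only then the program for controls. Commitment is therefore post-randomization, and undefined in the control arm at every outcome time point.

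**Size of a spurious contrast, median split.** Assume zero true program effect, a standard normal commitment score A, and correlation r between A and the outcome an employee would have had without the program. The documents do not give r, so a range is shown. The mean of a standard normal above its median is 0.798, hence:

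- high commitment − all controls = 0.798 × r
- high − low commitment = 2 × 0.798 × r

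| r (assumed) | High vs all controls (SD) | High vs low (SD) |
|---|---|---|
| 0 | 0 | 0 |
| 0.1 | 0.08 | 0.16 |
| 0.2 | 0.16 | 0.32 |
| 0.3 | 0.24 | 0.48 |

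A negative r gives the same sizes with the sign reversed.

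**Tertiles.** The mean of the top third of a standard normal is 1.091. The top tertile against all controls shows +0.11, +0.22 and +0.33 SD at r = 0.1, 0.2 and 0.3. The middle tertile shows 0 and the bottom tertile the mirror image, which is the shape of a dose-response.

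**False-positive rates under zero effect.** Simulation with 32 organizations of 20 per arm, ICC 0.09, cluster-robust standard errors and 2,000 replicates:

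| r (assumed) | Top tertile vs all controls | Commitment trend within intervention arm | Intention-to-treat contrast |
|---|---|---|---|
| 0 | 5% | 4% | 4% |
| 0.1 | 16% | 69% | 5% |
| 0.2 | 51% | >99% | 6% |
| 0.3 | 87% | 100% | 5% |

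The intention-to-treat contrast keeps its nominal error rate throughout; the commitment contrasts do not.

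**Does a complier-average estimate solve it?** Let p be the share of the intervention arm above a task threshold, d1 the effect in them and d0 the effect in those below it. The intention-to-treat effect is p × d1 + (1 − p) × d0. The instrumental estimate divides this by p, giving d1 + d0 × (1 − p)/p. It equals d1 only if d0 = 0, the exclusion restriction. The protocol expects otherwise: psychoeducation goes to all participants, employees receive and are asked to answer colleagues' messages, and the Background expects job resources to rise across the organization. With d0 > 0 the estimate is too large.

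**The case against.** The case for leaving the plan alone has substance.

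- **The analysis is peripheral.** It is called potential, no confirmatory or causal claim is attached to it, and the primary analysis is intention-to-treat. This stands and limits the severity. A reader might infer that the primary result is compromised; it is not.
- **The bias is not certain.** A reader might infer that a false dose-response must appear. The documents give no correlation between commitment and prognosis. At r = 0 there is no bias, and if less engaged staff did more of the tasks the gradient would run the other way.
- **The size is easily overstated.** One might set the 0.32 SD high-versus-low difference at r = 0.2 beside the planned 0.30. But 0.30 is an intervention-versus-control effect, and the like-for-like figure is 0.16 SD. If r refers to change in the scale, the results are in SDs of change; at an assumed test-retest correlation of 0.7 that SD is √(2 × 0.3) = 0.77 outcome SD, so 0.32 becomes 0.25 and 0.16 becomes 0.12. The counts are also small (six list sessions and at least three messages under Table 1), so normality is only an approximation.
- **The baseline factors.** A reader might infer from the word stratified that the effect of baseline work engagement or gratitude will be judged from separate strata without an interaction test. The sentence does not exclude such a test, and that detail commonly belongs in an analysis plan not shown here. It is no finding.

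None of this supplies a randomized comparator for the commitment strata. That defect lies in what the article states, since it names the variable and calls the analysis a subgroup analysis; it is not a detail left to another document.

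**Conclusion.** The point holds. Degree of commitment is not a valid subgroup factor in this trial: it is measured after allocation and exists only in the intervention arm during follow-up, so an effect stratified by it has no randomized comparator. It can mimic a dose-response when commitment correlates positively with prognosis.

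That structural conclusion needs no assumption. The sizes do: they rest on zero true effect, an approximately normal commitment score and an assumed r of 0.1 to 0.3. Against all controls the spurious median-split effect is then roughly a quarter to four fifths of the planned 0.30 (0.08/0.30 = 0.27; 0.24/0.30 = 0.80).

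Severity is minor to moderate.

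**What to change.** 1. Remove degree of commitment from the list of subgroup factors. Report the numbers of lists and messages as descriptive adherence data for the intervention arm, and state that any association with outcome is non-causal.
2. Keep only baseline variables (initial UWES and GAWS scores) as effect modifiers, preferably tested as arm-by-baseline interactions in the full model. This second part is a clarification.
3. If an estimate among those who take up the program is wanted, a complier-average effect should be at most an exploratory sensitivity analysis. It should carry a statement that spillover within organizations and psychoeducation sent to all participants strain the exclusion restriction and would tend to overstate the effect.

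The cost is a few lines of text; the optional model can be fitted in Mplus, which is already planned. The price is that the trial will have no headline estimate by commitment level.

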#### Data monitoring

Due to limited human resources, a Data Monitoring Committee (DMC) consisting of the first author (YK) and coordinator will be established at each organization. The DMC will discuss at each organization three months after randomization to review the participation rates and reasons for study dropouts. Data and Safety Monitoring Board (DSMB) will be prepared to monitor recruitment progress and data collection (e.g., percentage completing each follow-up) independently of sponsors and without competing interests.

#### Patient and public involvement statement

Partnering with people involved in the study is an ethical imperative for improving the study’s quality. In this study, working employees will be the intervention’s main target, and their collaboration in the process of program development will be important. In this context, we conducted a preliminary study to seek input from workers, which was reflected in the intervention program. However, these workers were not involved in the conception, design, and writing of the protocol paper.

#### Dissemination of research findings

This study’s findings will be submitted to peer-reviewed journals for publication following CONSORT guidelines for cRCTs. Participants will be notified of conference presentations and publications.

## Discussion

To the best of our knowledge, this study will be the first cRCT to investigate the effects of gratitude intervention on work engagement. Compared with other psychological interventions, gratitude interventions have several strengths in terms of implementation: the objectives of the exercises are easy to understand and implement; it does not require much time or expense; they tend to have lower dropout rates; and they do not require experts in psychology [39, 57]. Although implementation difficulties have been common in previous interventions targeting work engagement [6], gratitude intervention may be suitable even for workers who have limited time to devote to the tasks.

This study will have several limitations. First, because all data will be collected using a self-reported questionnaire, measurement errors and information bias could be introduced. Second, generalizability will be limited because snowball sampling will be used instead of random sampling. Third, due to the intervention's nature, it is not possible for both the intervention implementer and participants to be blind to group assignments.

## Data Availability

Upon publication of the results, the datasets generated and/or analysed during the current study will be available from the corresponding author on reasonable request.

## Abbreviations

JD-R model: Job demands-resource model
RCT: Randomized controlled trial
UMIN-CTR: University Hospital Medical Information Network Clinical Trials Registry
UWES: Utrecht Work Engagement Scale
GAWS: Gratitude At Work Scale
GSES: General Self-Efficacy Scale
SOCS: Sense Of Coherence Scale
BJSQ: Brief Job Stress Questionnaire
TOMH well-being-24: The University of Tokyo Occupational Mental Health well-being scale
K6: Kessler's psychological distress scale
WHO-HPQ: Health Performance Questionnaire
ICC: Intraclass correlations
CONSORT: Consolidated Standards of Reporting Trials
LGM: Latent growth modeling
CFI: Comparative fit index
TLI: Tucker–Lewis index
RMSEA: Root mean square error of approximation
ITT: Intention-to-treat
DMC: Data Monitoring Committee
DSMB: Data and Safety Monitoring Board
